#### Secondary outcomes

The ID of occlusion will be analyzed by the same method as for the primary objective.The number of cases of septic shock and bronchopulmonary dysplasia will be analyzed using GLMM, taking into account the duration of stay in the ICU for each patient. The model will be identical to that used for the primary objective.The duration of oxygen therapy, of mechanical ventilation, and of parenteral nutrition will be analyzed using the linear mixed model. The ICU, the period, and the device will be considered as fixed effects and the ICU × interaction period as a random effect. In the case of non-normal model residuals, we will use a non-parametric test without taking the design into account (Mann-Whitney U test).

Cost data will be analyzed using Stata®. Depending on normality test results, mean costs will be compared across groups using Student’s *t*-test or non-parametric bootstrap. A GLM model and a Generalized Gamma model will be used with child characteristics at baseline as regressors and considering fixed effects for the device (standard infusion system or Edelvaiss® Multiline NEO) and the ICU. Cost-effectiveness will be established and ICER estimated, retaining the number of CRB incidents as health outcomes. The 95% confidence interval for ICER will be computed using Fieller’s method or the bootstrap method.

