## Background

Catheter-related bacteremia (CRB) is the most frequent nosocomial infection in neonatal intensive care unit (NICU) patients, especially for very preterm infants whose weight is very low. The incidence density (ID) of CRB is estimated at 18.5 per 1000 catheter-days for infants under 29 weeks’ gestation, according to the criteria of the monitoring Network of Néocat [1]. CRB occurs after a few days or weeks of infusion [1]. Infection is the most common serious complication of central venous catheters (CVCs).

Nosocomial CRB in NICUs contributes significantly to hospital morbidity, for example, patent ductus arteriosus, prolonged ventilation, prolonged intravascular access, bronchopulmonary dysplasia, and necrotizing enterocolitis [2]. Leroyer et al. [3] completed a study in a French NICU and estimated that infected neonates stayed on average 5.2 days more in hospital than uninfected neonates. According to this study, infections cost on average $10,440 per infected case [3, 4]. Moreover, infections (late-onset and early-onset sepsis) in very preterm infants are associated with a higher risk of adverse neurodevelopment at the age of five years [5].

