### Study procedure

The infants’ healthcare providers will decide the date of insertion of the CVC according to NICU protocol. The choice of standard infusion system and Multiline NEO will be made randomly and will be connected to the CVC. The investigators will ensure daily that randomization is respected. The infusion system (standard or Multiline NEO) will be changed according to the manufacturer’s instructions throughout the patient inclusion period. The duration of use of the device is from the time of CVC insertion until catheter removal. Each intervention on the line (drug infusion, infusion rate, etc.), the catheter, and its dressing are recorded prospectively throughout the study period.

Three visits are planned in the study protocol:Visit 1 at the time of CVC insertion and onset of infusion (standard or Multiline NEO).Visit 2: at the withdrawal of CVC and infusion system (standard or Multiline NEO). The date and time of removal of the device, justification for CVC withdrawal (catheter removal, end of hospitalization, etc.), number of CRB incidents within the period of use of the device, number of occlusions of infusion devices and number of infusion days, and number of septic shock incidents defined by the use of vasoactive drugs will be recorded.Visit 3: at the end of the infant’s hospitalization. The total duration of oxygen therapy, mechanical ventilation, and parenteral nutrition, rate of chronic lung diseases, and the total length of hospital stay (including hospitalization outside the NICU) will be recorded.

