#### Secondary outcomes

Number of occlusions of the infusion system defined by an acute increase in infusion pressure recorded by the pump not due to accidental kinking of the line or CVC and requiring a specific intervention by the nurse (line-flushing or change of the line or CVC).Number of septic shock events defined by the occurrence of shock (low blood pressure, tachycardia, decrease in diuresis, capillary refill time > 3 s) in a context of sepsis, and the need for vasoactive drugs.Total duration of oxygen therapy calculated from inclusion of the patient in the study until the end of hospitalization. Need for oxygen therapy is defined by O_2_ administration to target arterial oxygen saturation between 90 and 96%.Total duration of intubation and mechanical ventilation determined from inclusion of the patient in the study until the end of hospitalization.Total duration of parenteral nutrition determined from inclusion of the patient in the study until the end of hospitalization. Parenteral nutrition is stopped (and CVC retrieved) when enteral feeding is above 120 ml/kg and caloric intake is above 100 kcal/kg.Presence or absence of chronic lung disease determined from inclusion of the patient in the study until the end of hospitalization. Chronic lung disease is defined by a need for O_2_ supplementation to maintain SpO2 > 90% at a postconceptional age > 36 weeks.Direct costs, including components of the infusion lines (considering their replacement in case of CRB), nursing time, biological tests to identify CRB (blood culture, catheter culture), management of bacteremia, extra-time in the ICU, and increased overall length of stay in the case of CRB. Costs will be accounted for during child hospitalization. Indirect costs (e.g., presence/absence of parents) and costs induced by child handicap following a CRB are beyond the scope of the study.

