#### Primary outcome

The ID of CRB, expressed as the number of cases of CRB per catheter × days, will be estimated and compared for each of the two devices. The generalized linear mixed model (GLMM) will be used with the number of CRB incidents as dependent variable. The GLMM model will be parametrized with a log linear link function, a Poisson distribution, and the logarithm of catheter duration as the offset variable. To take into account the cluster crossover design, we will consider the device (standard infusion system or Edelvaiss® Multiline NEO), the period, and the ICU as fixed effects and the ICU × interaction period as a random effect as recommended by Turner et al. [19]. Effect size will be estimated by relative risk reduction with a 95% confidence interval.

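### Bronchopulmonary dysplasia, a yes/no status, is to be analysed as a Poisson rate over ICU stay, and the denominator for septic shock does not match the visit at which shock is listed

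*Protocol article*

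**What the plan says.** All references are to the protocol article.

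- **Analysis.** Statistical analysis, Secondary outcomes, deals here with case counts and states that "septic shock and bronchopulmonary dysplasia will be analyzed using GLMM, taking into account the duration of stay in the ICU for each patient". It then adds: "The model will be identical to that used for the primary objective".
- **Primary model.** Statistical analysis, Primary outcome, specifies "a log linear link function, a Poisson distribution, and the logarithm of catheter duration as the offset variable". Device, period and ICU are fixed effects, and the ICU-by-period interaction is random.
- **Lung outcome.** Outcome measures, Secondary outcomes, defines it as "Presence or absence of chronic lung disease determined from inclusion of the patient in the study until the end of hospitalization", by oxygen need "at a postconceptional age > 36 weeks". The outcome list has no separate entry for bronchopulmonary dysplasia, so the two terms are read here as one outcome. It is recorded at Visit 3, at the end of hospitalization.
- **Septic shock.** The outcome list gives "Number of septic shock events defined by the occurrence of shock", with clinical signs, a context of sepsis and the need for vasoactive drugs, and no time window. Study procedure places the count at Visit 2, at catheter withdrawal: "number of septic shock incidents defined by the use of vasoactive drugs will be recorded". Shock is not among the Visit 3 items.
- **Occlusion.** It is also listed at Visit 2, and it is analysed by the primary method.
- **Length of stay.** Background reports that "infected neonates stayed on average 5.2 days more in hospital than uninfected neonates". The cost outcome also counts extra ICU time in the case of CRB.

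**The concern.** The model is fixed by reference to one built for a different kind of outcome. CRB can recur and accrues over catheter time. Chronic lung disease can be present at most once per infant and is read at a set age. Dividing it by ICU-days changes the question from whether the device alters the chance of the disease to how many cases occur per day of ICU care. The Poisson variance also exceeds the true variance of a yes/no outcome.

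For septic shock, the numerator appears to be collected over catheter time while the denominator runs over the whole ICU stay. Occlusion, counted at the same visit, gets catheter-days, and no reason is given for the difference.

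At stake are the interpretability of two secondary estimates and the precision of one of them. The primary comparison is not touched.

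**Working it through.** **The plan's own figure.** None is given for these two outcomes. The sample size concerns CRB only, and it reproduces. Comparing 18.5 with 9.25 per 1000 catheter-days, two-sided 5%, 80% power, gives 2510 catheter-days per group. 2510/21 = 119.5, so 120 infants. The design effect is 1 + 34 × 0.01 − 35 × 0.005 = 1.165, and 120 × 1.165 = 139.8, so 140 per group. That group size is used in step 4.

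**1. Which model is meant?** There are three readings of the analysis text.
- ICU stay replaces catheter duration as the offset. This is the natural reading.
- ICU stay enters as a covariate. This adjusts for something measured after allocation.
- The model is literally identical, with a catheter-day offset. This contradicts the wording on ICU stay.

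All three keep a Poisson likelihood for a binary outcome.

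**2. Standard error.** For n infants with risk p, the variance of the log risk is 1/(np) under Poisson and (1−p)/(np) under binomial. The ratio of standard errors is 1/√(1−p). The protocol gives no risk, so p is assumed:

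| Assumed risk p | 1/√(1−p) | SE too wide by |
|---|---|---|
| 0.20 | 1.118 | 12% |
| 0.30 | 1.195 | 20% |
| 0.40 | 1.291 | 29% |
| 0.50 | 1.414 | 41% |

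The ICU-by-period random effect can only add variance, so it cannot correct this.

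**3. Effect of the ICU-day denominator on the ratio.** Assume a mean ICU stay of 45 days without the disease and d extra days with it. The reported ratio is [p₁/(45 + p₁d)] / [p₀/(45 + p₀d)]. Take p₀ = 0.40 and p₁ = 0.30, a true ratio of 0.75.
- d = 14: (0.30/49.2)/(0.40/50.6) = 0.771.
- d = 28: (0.30/53.4)/(0.40/56.2) = 0.789.

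For p₀ from 0.20 to 0.50 and d from 7 to 28, the range is 0.756 to 0.797.

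**4. Cost in power.** 2000 simulated trials per scenario, 140 infants per arm, no clustering, gamma-distributed stay with mean 45 days before any extra days. The comparator is a risk model without offset and with robust standard errors.

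| Scenario (assumed) | Rejects: Poisson with ICU-day offset | Rejects: risk model |
|---|---|---|
| 40% vs 40%, d = 14 | 0.9% | 4.0% |
| 40% vs 30%, d = 0 | 25% | 40% |
| 40% vs 30%, d = 14 | 17% | 39% |

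In the first row the model's own standard error averages 0.190 against an empirical 0.140. The second row shows that power is lost even if the disease adds no ICU days.

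**5. Bias if the device shortens ICU stay.** Expected CRBs per infant are 0.0185 × 21 = 0.3885 with the standard system. Halving this averts 0.194 per infant. At 5.2 days each, mean stay differs by 0.194 × 5.2 ≈ 1.01 days. For an outcome that the device does not affect, the per-ICU-day ratio is L/(L − 1.01). This gives 1.035, 1.023, 1.017 and 1.011 for assumed mean stays L of 30, 45, 60 and 90 days.

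**6. Septic shock.** Visit 2 lists CRB, occlusion and shock together. Visit 3 lists the respiratory, nutrition and length-of-stay items, but not shock. If the lists are complete, shock is observed over catheter time, and ICU-days are the wrong exposure. The Visit 2 text defines shock by vasoactive drug use alone. The outcome list also requires signs of shock and a context of sepsis.

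**The case against.** Much can be said on the other side.

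- **The error is conservative.** Too wide a standard error creates no false positives, and the trial is sized only for CRB. This stands and limits the severity. A reader might infer that the test is invalid in the sense of excess type I error; step 4 shows the opposite.
- **ICU stay may be meant to allow for unequal observation.** That would be reasonable for recurring events. Here, status is determined up to the end of hospitalization, and Visit 3 covers hospital stay outside the NICU, so ICU-days are not the observation time.
- **The offset is not stated.** The text says only that ICU stay is taken into account. True, but the binary outcome is mis-modelled on every reading in step 1.
- **A large bias from shortened stay is not supported.** A reader might apply the 5.2 days to a whole arm, which at a 60-day mean would give 60/54.8 = 1.09. That figure is extra hospital stay per infected infant. Spread over the infections averted, it is about one day.
- **The documents do not say that lung disease or shock lengthens ICU stay.** They say so only of infection and CRB. The pull toward 1 in step 3 is therefore conditional.
- **The recording window for shock is inferred.** The outcome definition gives none, and the phrase limiting events to the period of device use is attached to CRB. A reader might take it as stated that shock is counted only to catheter removal; it follows only from the visit lists.
- **Catheter-days are also measured after allocation.** This stands. Using them for shock matches events to exposure but does not remove that dependence. A Poisson count model for shock is itself acceptable.
- **The Visit 2 wording on shock may be shorthand.** This is possible, since both descriptions include vasoactive drugs, but as written they differ.

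**Conclusion.** The point holds for bronchopulmonary dysplasia without any assumption about stay: the analysis text prescribes a Poisson rate model for an outcome that the same article defines as present or absent. The standard error is too wide by about 12% to 41% for assumed risks of 20% to 50%, and power is lost. Attenuation of a ratio of 0.75 to about 0.76 to 0.80 follows only if the disease lengthens ICU stay.

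For septic shock, the mismatch between ICU stay and the visit at which shock is listed is a fair inference that needs clarifying, not an established error. Bias from the device shortening ICU stay is about 1% to 3.5% on the protocol's own figures, for assumed mean stays of 90 down to 30 days, and is not a serious concern.

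Severity is moderate. Only secondary outcomes are affected, and the conclusion on CRB does not depend on them.

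**What to change.** 1. **Chronic lung disease.** Analyse it as binary with no stay offset, keeping device, period and ICU as fixed effects and ICU by period as random. A logistic or log-binomial mixed model would do. Poisson with robust variance is an alternative, but if the variance is clustered on ICU by period it rests on only 4 × 2 = 8 cells. Use one name for the outcome throughout.
2. **Septic shock.** Keep the count model. State the period over which shock is recorded and make the offset match it: log catheter-days, as for occlusion, if recording stops at catheter withdrawal.
3. **Definition of shock.** Reconcile the Visit 2 wording with the outcome list so that one definition is recorded and analysed.

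Items 1 and 2 cost a few lines of analysis text, need no new visit, and should be settled before analysis. Item 3 is equally cheap if the Visit 2 wording is shorthand. If the reconciled definition needs signs that the case report form does not capture, there is a data-collection cost, which the article does not allow one to judge.

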### Sample size estimation

To meet the main objective, we will compare the incidence density (ID) of CRB in the two groups (Multiline NEO and standard infusion system). Determination of the initial risk level is based on data for patients under 29 weeks’ gestational age following the criteria of the Néocat network. With the standard infusion system, the CRB rate is estimated at 18.5 per 1000 catheter-days for this population. It is estimated that the Multiline NEO, correctly implemented, should reduce this rate by 50%. The average duration of catheterization is estimated at 21 days in very low-birth-weight infants. As regards the 50% reduction in CRB rate, there are even more optimistic results to be found in the literature with strategies based on structured methods to improve the care process (bundles and checklists). Erdai et al. [16] showed a 77% reduction in the rate of catheter-related infection with the use of such strategies.

As a result, with a combination of the Edelvaiss® Multiline NEO device and a training program before use, we can assert that the assumption of a 50% decrease in CRB is realistic.

Using a chi-square test at 5% significance level, with 80% power, 2510 catheter-days are required for each group. Given an average duration of 21 days of catheterization, it is therefore necessary to recruit 120 subjects per group (per drug infusion system) without clustering correction. To include clustering effects, we will use the method proposed by Giraudeau et al. [17], estimating the intra-class correlation coefficient (ICC) at 0.01 based on a previous cluster-randomized study in an ICU [18] and the inter-period correlation coefficient at 0.005 (half of ICC as recommended by Giraudeau et al. [17]). This yields 35 as the required number of subjects for each ICU and each period (design effect of 1.16). We therefore plan to recruit a total of 280 patients (140 per group).

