### Statistical analysis

Data will be analyzed using SAS software (SAS Institute Inc., Cary, NC, USA) and all statistical tests will be performed with a two-tailed alpha risk factor of 0.05. Baseline characteristics will be described for each group. Quantitative variables will be expressed as mean (standard deviation), median (interquartile range), and range. Qualitative variables will be expressed as frequencies and percentages. Normality of distribution will be assessed graphically and using the Shapiro-Wilk test.

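### With non-normal residuals, the three duration outcomes switch to a Mann-Whitney test that ignores the cluster-crossover design, and the cost models also omit part of that design

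*Protocol article*

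**What the plan says.** All references are to the protocol article.

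- **Statistical analysis, Secondary outcomes (durations).** The first analysis is a linear mixed model with ICU, period and device as fixed effects and ICU × period as a random effect. The fallback is then stated: "In the case of non-normal model residuals, we will use a non-parametric test without taking the design into account (Mann-Whitney U test".
- **Statistical analysis, Secondary outcomes (costs).** "Depending on normality test results, mean costs will be compared across groups using" Student's t-test or a non-parametric bootstrap. A GLM and a Generalized Gamma model follow, with baseline characteristics as regressors and "considering fixed effects for the device (standard infusion system or Edelvaiss® Multiline NEO) and the ICU". Neither period nor ICU × period is named.
- **Statistical analysis (general).** "all statistical tests will be performed with a two-tailed alpha risk factor of 0.05". Normality is to be judged graphically and by the Shapiro-Wilk test.
- **Statistical analysis, Primary outcome.** The Poisson mixed model for catheter-related bacteremia (CRB) keeps device, period, ICU and ICU × period.
- **Sample size estimation.** The CRB sample size is inflated for clustering by a design effect of 1.16, to 35 infants per ICU and period, 280 in all.

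**The concern.** The unit of randomisation is the ICU, which then changes device between periods. Infants in the same ICU and period share staff, case mix and practice. If that shared component differs between the two periods of an ICU, it adds directly to the device contrast and does not shrink as more infants are recruited in the cell. A Mann-Whitney test on 140 versus 140 infants has no term for it.

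The fallback may well become the analysis that is reported. Durations are bounded at zero and are often right-skewed, and a Shapiro-Wilk test on about 280 residuals is sensitive: in simulated lognormal samples of 280 with a log-scale SD of only 0.2 it rejected normality about 94% of the time. That the switch is likely is a judgement, because the documents give no distributions for these outcomes.

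At stake are the p-values for three clinical secondary outcomes and for the cost comparison.

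**Working it through.** **1. The plan's own figures reproduce.** Inputs from Sample size estimation: 0.0185 versus 0.00925 per catheter-day (18.5 per 1000, halved), two-sided 5%, 80% power, 21 days per infant, ICC 0.01, inter-period correlation (IPC) 0.005.

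- Pooled two-proportion formula: n = [1.960·√(2 × 0.013875 × 0.986125) + 0.842·√(0.0185 × 0.9815 + 0.00925 × 0.99075)]² / 0.00925², which rounds up to 2510. This matches "Using a chi-square test at 5% significance level, with 80% power, 2510 catheter-days are required for each group".
- 2510 / 21 = 119.5, so 120 infants per group.
- Design effect with m = 35 per ICU-period: DE = 1 + (m − 1)·ICC − m·IPC = 1 + 0.34 − 0.175 = 1.165 (printed as 1.16).
- 120 × 1.165 = 139.8, so 140 per group, or 35 in each of eight cells.

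**2. Type I error of a test that ignores the design.** If the true variance of the contrast is DE times what the test assumes, the error is approximately 2·[1 − Φ(1.96/√DE)]. This was checked by simulating null trials of 4 ICUs × 2 periods × 35 infants (4,000 to 6,000 per scenario in each run). Mann-Whitney depends only on ranks, so the results hold equally for lognormal durations.

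| ICC / IPC | DE | Formula | Simulated |
|---|---|---|---|
| 0.01 / 0.005 (the plan's values) | 1.165 | 6.9% | 6.2–7.3% |
| 0.02 / 0.01 (assumed) | 1.33 | 8.9% | 8.6–8.9% |
| 0.05 / 0.025 (assumed) | 1.825 | 14.7% | 14–15% |
| 0.10 / 0.05 (assumed) | 2.65 | 22.9% | 21–23% |
| 0.05 / 0.04 (assumed) | 1.30 | 8.6% | 8.4% |
| 0.05 / 0.05 (assumed, stable ICUs) | 0.95 | 4.4% | 4.8% |
| 0.10 / 0.10 (assumed, stable ICUs) | 0.90 | 3.9% | 4.1% |

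The last two rows have no ICU × period variation, and the test is then slightly conservative.

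**3. Which omitted term matters.** Adding a common period shift of 0.3 SD gave 7.1% at ICC 0.01 and 14.4% at ICC 0.05 (IPC half the ICC), almost the same as without it. Each centre recruits equal numbers in both periods, so a common shift largely cancels. The harm comes from dropping ICU × period.

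**4. Costs.** Simulated type I error at ICC 0.01, 0.05 and 0.10 (IPC half the ICC):

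- unadjusted t-test on lognormal costs: 5.8%, 11.2%, 17.4%;
- device and ICU fixed only, log scale: 7.4%, 16.6%, 24.6%.

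**5. Which remedies work.**

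- Eight cell means, less intercept, three ICU terms, one period term and one device term, leave 8 − 6 = 2 degrees of freedom.
- Rank analysis of the eight cell means, adjusted for ICU and period, t on 2 df: 4.5–5.8% in every scenario.
- Mixed model with the right terms but patient-level residual df (272): still 8.8% and 11.9% at ICC 0.05 and 0.10. At ICC 0.01 the ICU × period variance was estimated as zero in 57% of trials.
- Resampling infants within ICU-period cells (by its normal-theory equivalent): about 7%, 16% and 25–26% at ICC 0.01, 0.05 and 0.10. It holds the cell means fixed and so removes the variance at issue.
- Re-randomisation offers no way out: four ICUs split two and two give only 6 allocations, so p < 0.05 cannot be reached.

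**The case against.** The strongest reply is about size and scope, and much of it stands.

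- **Primary result.** A reader might infer that the trial's main conclusion is at risk. It is not. The CRB model keeps the full design, and occlusion, septic shock and bronchopulmonary dysplasia use that same model.
- **Sample size.** A reader might see a contradiction with the clustering correction in the sample size. That correction was made for CRB only, so there is an inconsistency of principle, not an error in the outcome that was sized.
- **Magnitude.** A reader might quote 14% or 23% as the error rate. The only correlations in the document are 0.01 and 0.005, and they give about 7%. The larger figures depend on assumed ICCs, and with stable ICU differences the error runs the other way.
- **Trigger.** A reader might take the switch as certain. The rule concerns model residuals, judged partly by graph, and the mixed model comes first.
- **Costs.** A reader might say that all cost analyses ignore the design. The regressions include ICU, and the article does not say how the bootstrap resamples, which may properly be left to the full plan. What can be criticised is the t-test without ICU or period and the two terms missing from the regressions.

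What does not yield is the fallback sentence itself. It says outright that the design will be set aside, so it is not a detail left to an analysis plan.

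**Conclusion.** The point holds for secondary and cost outcomes. The protocol fixes a rule under which a distributional finding removes the ICU × period structure from the analysis of three durations. At the plan's own correlations, the nominal 5% test runs at about 6.5–7%, a modest inflation. It would reach 14–15% at 0.05/0.025 and 22–23% at 0.10/0.05 if durations cluster that strongly, and would fall a little below 5% if ICUs differ but do not change between periods. Because no ICC for durations is given, neither the direction nor the size of the error can be fixed in advance, which is itself a reason not to rely on the test. The figures assume 35 infants in each of eight cells and normally distributed ICU and ICU × period effects on a latent scale.

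**What to change.** **Durations.** Delete the Mann-Whitney fallback. Keep device, period and ICU fixed with ICU × period random whatever the residuals look like, and handle skewness inside that structure. Options are log(duration + 1) or ranks in the same mixed model, or a rank analysis of the eight cluster-period means adjusted for ICU and period. Name one in advance. State that the device effect is tested on the 2 df available for ICU × period, not on patient-level residual df.

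**Costs.** Add period and ICU × period to the GLM and Generalized Gamma models with the same small-sample inference, and take the device contrast from them in place of the unadjusted t-test. If a bootstrap is retained, it should not resample within ICU × period cells.

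**What it costs.** Only the wording of the analysis changes, and no new data are needed. The price is precision: at the same standard error, the 95% multiplier rises from 1.960 to 4.303, an interval about 2.2 times as wide (4.303 / 1.960), with low power for these outcomes. That reflects what four clusters can actually show.
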